#### Sample Size

The total number of required study participants was calculated for the primary outcome (decreased maximal pain after 8 months). The calculation was based on several assumptions. First, we considered the expected proportion of participants who decreased their maximal pain after 8 months in the intervention group. We estimated that 30% of the intervention group would decrease their maximal pain after 8 months based on previous research with CBT, in which approximately 50% of participants were pain free immediately after the intervention [79]. Second, we calculated the expected proportion of participants whose maximal pain would decrease after 8 months in the control group. In previous CBT studies, approximately 25% of control participants reported being pain free when the intervention ended [79]. Since only girls with a long duration of abdominal pain were included in the present study, we estimated that the placebo effect would be smaller and that 10% of the girls in the control group would report decreased maximal pain at the 8-month follow-up. Third, dropout is a common problem that can bias outcomes. A 20% to 50% dropout rate is commonly reported in studies of participants with long-lasting pain [80]. In the present study, a 20% dropout rate was estimated.

With a power of 80% and a significance level of .05, we calculated the sample size to be N=150 (75 intervention + 75 control participants), including a 20% dropout. To decrease bias, a minimum of 50 participants in each group is recommended in trials studying intervention effects on pain, according to previous literature [80].

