#### Inclusion Criteria

Inclusion criteria followed the diagnostic criteria for childhood functional abdominal pain in Rome III [2]: (1) episodic or continuous abdominal pain at least once per week for at least 2 months before diagnosis; (2) insufficient criteria for other FGIDs; and (3) no evidence of an inflammatory, anatomic, metabolic, or neoplastic process that explains the patient’s symptoms.

The following criteria were tested to exclude other illnesses: (1) physical examination including normal growth pattern and (2) laboratory screening, including serological screening with immunoglobulin A antibodies against type 2 (tissue) transglutaminase (TGA-IgA), complete blood cell count, erythrocyte sedimentation rate or C-reactive protein, and urine analysis. A fecal calprotectin test was also included if the girl reported symptoms such as diarrhea.

Diagnostic criteria for IBS in Rome III [2] were used. First, at least once per week for at least 2 months before diagnosis, the patient must have had abdominal discomfort or pain associated with 2 or more of the following at least 25% of the time: (1) improved with defecation, (2) onset associated with a change in the frequency of stool, or (3) onset associated with a change in the form (appearance) of stool. Second, there must be no evidence of an inflammatory, anatomic, metabolic, or neoplastic process that explains the patient’s symptoms.

The following criteria were tested to exclude other illnesses: (1) physical examination including normal growth pattern and (2) laboratory screening including serological screening with TGA-IgA, complete blood cell count, erythrocyte sedimentation rate or C-reactive protein, and urine analysis. A fecal calprotectin test was also included if the girl reported symptoms such as diarrhea.

Persistent pain after examination at the pediatric center was measured with a pain diary at baseline. Girls who reported one or more episodes of pain with a pain score of 4 or higher on the faces pain scale-revised (FPS-r) [76,77] during a full week were eligible for the study.

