#### Primary Outcome Measure

The primary outcome is the proportion of girls in each group who have reduced maximal pain, measured immediately after the intervention (8-month follow-up) with the FPS-r [76,77] in a pain diary in which the girls register their abdominal pain 3 times a day for 1 week. The psychometric features for the FPS-r are reported to be good [77].

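### The planning rates of 10% and 30% for any fall in maximal pain are set below the pain-free rates they are derived from, so the stated 80% power is unsupported

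*Protocol article*

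**What the plan says.** All places are in the Methods of the protocol article unless stated.

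- Primary Outcome Measure: "The primary outcome is the proportion of girls in each group who have reduced maximal pain". It is read at the 8-month follow-up from a one-week FPS-r diary. No minimum size of reduction is given.
- Inclusion Criteria: "Girls who reported one or more episodes of pain with a pain score of 4 or higher" on that scale during the baseline diary week were eligible.
- Sample Size, intervention arm: "We estimated that 30% of the intervention group would decrease their maximal pain after 8 months". The basis is CBT research in which about 50% were pain free after treatment.
- Sample Size, control arm: in the earlier CBT studies "approximately 25% of control participants reported being pain free when the intervention ended". From this, and citing the long duration of pain in the girls recruited, "we estimated that the placebo effect would be smaller and that 10% of the girls in the control group would report decreased maximal pain".
- Sample Size, result: 80% power, significance level .05, N=150 (75 per arm) including 20% dropout.
- Statistical Analysis: the primary comparison is a Fisher exact test, two-tailed at .05.
- Results: 121 girls were allocated, 64 to intervention and 57 to control.

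**The concern.** The plan moves from a strict outcome (no pain) to an easier one (less maximal pain than before) and lowers the expected rates in both arms. An easier outcome cannot have a lower rate in the same girls. The one reason given for the control rate is long pain duration with a smaller placebo effect. That could lower a pain-free rate. It does not account for the change of endpoint.

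Nor does it account for regression to the mean. Girls qualify on one week's diary, and success is a fall from that same week's maximum, so some will show a fall without any real change.

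At stake is how the result will be read. If the control rate is well above 10% and the difference stays at 20 points, the trial is weaker than stated, and a null result set against 80% power would be taken as stronger evidence of no effect than it is.

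**Working it through.** **1. The plan's own figure.** Inputs from Sample Size: p1 = 0.30, p2 = 0.10, two-sided 0.05, power 0.80. With the pooled formula

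n = [1.96·√(2·p̄·q̄) + 0.8416·√(p1·q1 + p2·q2)]² / (p1 − p2)², where p̄ = 0.20,

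n = [1.96·√0.32 + 0.8416·√0.30]² / 0.04 = (1.109 + 0.461)² / 0.04 = 61.6, so 62 per arm. Then 62 × 1.2 = 74.4, so 75 per arm and N=150. The arcsine formula gives 60 per arm, and 60 / 0.8 = 75. The arithmetic reproduces; the issue is the inputs.

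**2. Ordering of the two outcomes.** The baseline maximum is at least 4 for every girl. A pain-free girl has an 8-month maximum of 0, which is below 4, so she counts as reduced. Hence P(reduced) ≥ P(pain free) in the same girls. The plan has 10% against a cited 25%, and 30% against a cited 50%.

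**3. Control rate with no true change.** The documents give no mean, SD or between-week correlation, so these are assumptions: maximal score with mean 4 to 6, SD 2 to 3, correlation 0.3 to 0.9, a normal person level plus weekly noise, rounded to 0, 2, …, 10, keeping girls with baseline 4 or higher.

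| Reading | Range over the grid |
|---|---|
| Any fall, no true change | 18% to 53% |
| Fall of at least 4 points, no true change | about 0% to 29% |
| Any fall, true rise of 1 point after baseline | 3% to 41% |

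Under the first reading no cell comes down to 10%. Under the other two, some do.

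**4. Power of the planned test.** Exact two-sided Fisher power by full enumeration. Completers as planned: 75 × 0.8 = 60 per arm. Completers from the girls allocated: 64 × 0.8 = 51.2 and 57 × 0.8 = 45.6, so 51 and 46.

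| Control v intervention | 60/60 | 51/46 |
|---|---|---|
| 10% v 30% (plan) | 73% | 66% |
| 20% v 40% | 60% | 53% |
| 30% v 50% | 54% | 48% |
| 40% v 60% | 54% | 48% |
| 25% v 50% (cited pain-free rates) | 76% | 69% |
| 40% v 72% (plan's odds ratio kept) | 93% | 88% |

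The last row uses the plan's odds ratio, (0.30/0.70) / (0.10/0.90) = 3.86. At a 40% control rate the odds are 0.667 × 3.86 = 2.57, that is 72%.

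The first row separates the causes. At the plan's own rates the pooled z formula gives 79% with 60 per arm and the Fisher test 73%, so part of the gap to 80% comes from the test. The move to 66% comes from the recruitment shortfall. The control rate alone takes 73% to between 54% and 60% at 60/60, and only if the difference stays at 20 points.

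**The case against.** A reader might infer that a 10% control rate is unattainable. The documents do not support that. They give no size of reduction, and this is a condensed article whose full analysis plan may set one; with a required fall of 4 points, 10% lies within the simulated range. The Discussion also says baseline followed the summer holiday, when symptoms can be lower, so controls may drift upward, against regression to the mean. A rise of 1 point is enough in some cells. The cited rates come from other studies and another population. All of this stands. None of it appears in Sample Size as a reason for 10%.

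A reader might also infer that power is necessarily lost. It is not. Power depends on the difference as well as the control rate. At the cited 25% v 50% it is 76% with 60 per arm, slightly above the 73% at the plan's own rates, and with a constant odds ratio it is higher still.

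Nor are the girls strongly selected: one entry of 4 or higher in a week is a modest bar. The ordering argument needs only a baseline above zero.

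Finally, randomization protects the between-arm comparison from regression to the mean, the Statistical Analysis section already tests between arms, and a mixed model for change scores is planned. So the comparison is not biased by this. What remains is the justification of the rates and of the power.

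**Conclusion.** The point holds as a fault in the planning rates and the power statement, not in the validity of the comparison. The rates come from an outcome that does not match the endpoint and were moved in the direction that an easier endpoint does not allow without further argument. Under the reading in which any fall counts, 10% is implausible: 18% to 53% with no true change, on assumed distributions.

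The 80% figure is unsupported for two separate reasons. Its inputs are not justified for this endpoint, and the planned Fisher test does not deliver it even at those inputs (73% at 60/60, 66% at 51/46). The true power is unknown. It is about 48% to 60% if the 20-point difference persists at control rates of 20% to 40%, and 69% to 76% at the cited rates. The 51/46 figures assume that 20% of the allocated girls are lost.

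**What to change.** 1. Restate the power for the Fisher test with the 121 girls allocated, over control rates of about 10% to 40% and under both assumptions on the difference: a constant 20 points, and the cited 25% v 50%. State that a null result will not be read against 80% power.
2. Keep the primary endpoint. Name as its key supporting analysis the 8-month maximal FPS-r score compared between arms, adjusted for baseline maximum and age. Pain intensity and age at baseline are the minimization factors, and the full score uses more of the diary than a yes/no fall.

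The cost is a revised paragraph and one further analysis of data already being collected. The stated power will probably be less favourable.

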### Analyses

#### Statistical Analysis

The Just in TIME study follows the intention-to-treat paradigm. Complementary analyses will be performed per protocol and according to the number of sessions the participant attends.

For baseline statistics between the groups, descriptions will be constructed using frequencies and proportions for categorical data and means and standard deviations for continuous variables. Baseline characteristics will be compared using the Fisher exact test for dichotomous outcomes, the Mantel-Haenszel chi-square test for ordered categorical outcomes, and the Mann-Whitney U test or unpaired *t* test for continuous outcomes. A *P* value of <.05 for the 2-tailed test will be considered statistically significant for all outcomes. When deemed necessary, correction for multiple significance will be performed.

The primary outcome analysis will initially be performed using a Fisher exact test to evaluate differences between groups. To analyze the change in scores from baseline between groups for approximately normally distributed variables, a repeated-measures covariance pattern mixed model will be used, adjusting for significant differences at baseline. To identify predictive factors at baseline that might be associated with the primary outcome, a univariable logistic regression analysis followed by a stepwise multiple logistic regression analysis will be performed.

The distribution of continuous variables will be described using the mean and standard deviation or median and interquartile range. Categorical variables will be described with numbers and percentages.

Study participants who choose to leave the intervention before the study is finished are encouraged to complete all assessments. Missing data will be handled with multiple imputations or within the mixed model.

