## Results

Ethical approval was received in March 2016 and the data collection began in October 2016.

In total, 172 participants were recruited in 3 waves and the intervention was performed in 3 periods from 2016 through 2019. In summary, 121 girls were eligible and allocated. A total of 64 participants were allocated to the intervention group, and 57 participants were allocated to the control group. Data collection of the postintervention follow-ups are ongoing and the final 5-year follow-up will be completed by fall 2023. We expect to publish the first results of the study in the beginning of 2021.

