Several aspects of our trial design are worth noting as potential limitations. The timing of the intervention period followed the Swedish school year, which meant that we conducted the baseline measurement after the summer holiday, when the symptoms from FAPDs can be lower than at other times during the school year. This may have resulted in somewhat inflated exclusion rates, as some girls did not reach the inclusion criteria at the time point for inclusion. Moreover, due to the age of the target group, we need to rely on legal guardians to assist with data collection, which might influence the outcome. There is a possibility that girls with more engaged legal guardians could be overrepresented in the study groups. Intervention logistics, such as avoiding conflicts between the dance and yoga class and the participants’ school curriculum and offering the intervention in an easily accessible studio, are worth considering in future research and in dissemination plans if the activity is being implemented in usual care.

In addition, regarding the biomarker and physiological measures (saliva cortisol, feces, and accelerometer data), we cannot verify how meticulously the participants followed the prescribed guidelines.

The results from this study will broaden the knowledge of how nonpharmacological interventions can be valuable for overcoming the future challenge of reducing the burden of FAPDs for young girls and their families. Combined dance and yoga could be an example of an easy-access joyful intervention with promise as a complementary treatment.

To conclude, this randomized controlled study with 150 participants will investigate the effects of combined dance and yoga in girls with FAPDs. The primary aim is to study the effects of the intervention on abdominal pain, but several other aspects of FAPDs in young girls will also be studied. The results from this intervention study may provide useful information for caregivers in school health care, primary health care, and pediatric outpatient clinics.

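### The stated 80% power does not belong to the planned Fisher exact test (73% at 60 analysed per arm), and the article closes by describing 150 participants although 121 were allocated

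*Protocol article*

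**What the plan says.** The primary outcome is binary: whether a girl's maximal diary pain is reduced at the 8-month follow-up. The Sample Size section assumes "We estimated that 30% of the intervention group would decrease their maximal pain after 8 months" and that "10% of the girls in the control group would report decreased maximal pain at the 8-month follow-up". With 80% power and a .05 level it concludes: "we calculated the sample size to be N=150 (75 intervention + 75 control participants), including a 20% dropout". That section names no test or formula. It adds, citing earlier literature, that "a minimum of 50 participants in each group is recommended in trials studying intervention effects on pain".

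The Statistical Analysis section sets a two-tailed .05 criterion for all outcomes and names the primary test: "The primary outcome analysis will initially be performed using a Fisher exact test to evaluate differences between groups".

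The Results section reports that recruitment took place in three waves and that 121 girls were allocated: "A total of 64 participants were allocated to the intervention group, and 57 participants were allocated to the control group". The final paragraph of the Discussion says that "this randomized controlled study with 150 participants will investigate the effects of combined dance and yoga in girls with FAPDs".

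**The concern.** Two things do not fit together. First, the power claim and the primary test are both stated in this article but do not belong to each other. A Fisher exact test is more conservative than the normal-approximation test that 150 appears to rest on, so the planned analysis has less power than stated even if recruitment and retention go exactly to plan. Second, the trial allocated 29 fewer girls than its target (150 − 121, or 19%), yet the conclusion describes the trial by the target number, and neither the Results nor the limitations say what the shortfall does to power.

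At stake is how a non-significant primary result is read. Someone relying on the Sample Size section and the conclusion would take it as coming from a trial of 150 with a 20% chance of missing the target effect. For the trial as allocated, that chance under the planned test is between about 23% and 36%, depending on dropout.

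**Working it through.** **Inputs.** 30% v 10%, 80% power, .05 level, 20% dropout and 75 per arm (Sample Size); two-tailed Fisher exact test (Statistical Analysis); 64 and 57 allocated (Results).

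**1. Reproducing N=150.** The average proportion is (0.30 + 0.10)/2 = 0.20.

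- Pooled normal approximation: n = [1.960·√(2·0.20·0.80) + 0.842·√(0.30·0.70 + 0.10·0.90)]² / 0.20² = 61.6, so 62 per arm. 62 × 1.2 = 74.4, so 75 per arm and N=150 exactly. (62/0.8 = 77.5 would give 78 per arm, N=156.)
- Unpooled normal approximation: n = (1.960 + 0.842)² × 0.30 / 0.20² = 58.9, so 59 per arm. 59/0.8 = 73.75, so 74 per arm, N=148.
- With continuity correction: 72 per arm. 72/0.8 = 90, N=180; this does not reproduce.

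The stated figure is therefore consistent with an uncorrected normal-approximation (chi-square) calculation.

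**2. Exact power.** For analysed numbers n₁ and n₂, power is the sum, over all pairs (i, j), of Bin(i; n₁, 0.30) × Bin(j; n₂, 0.10), counting the pairs for which the two-sided P value is below .05. Expected numbers after 20% loss are:

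- Planned: 75 × 0.8 = 60 per arm.
- Allocated: 64 × 0.8 = 51.2 and 57 × 0.8 = 45.6.

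| Scenario | Analysed | Fisher exact | Uncorrected chi-square |
|---|---|---|---|
| 150 randomised, 20% lost | 60 / 60 | 73.0% | 80.2% |
| 121 randomised, none lost | 64 / 57 | 77.3% | – |
| 121 randomised, 20% lost | 51 / 46 | 66.3% | 71.0% |
| same, other roundings | 52 / 46 | 64.6% | – |
| same, other roundings | 51 / 45 | 63.6% | – |

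**3. What Fisher would have needed.** Power is 79.97% at 68 per arm and 80.7% at 69, so 69 analysed per arm. 69/0.8 = 86.25, so 87 randomised per arm, or 174 in total.

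**4. Type II error for the trial as allocated.** 100 − 77.3 = 22.7% with complete outcomes; 100 − 66.3 = 33.7% at 51/46 and 100 − 63.6 = 36.4% at 51/45.

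**5. The cited figure of 50 per group.** Both allocated arms (64 and 57) exceed it. Losing 8 of the 57 controls (14%) would leave 49 analysed; a 20% loss would leave about 46.

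**The case against.** The strongest reply is that nothing was miscalculated. 150 reproduces exactly, the Sample Size section does not claim that its power refers to a Fisher test, and sizing by a normal approximation before analysing with an exact test is a common mismatch. This stands: it would be wrong to infer an arithmetic error. But the same article names the Fisher test as the primary between-group analysis, so the 80% does not describe the planned analysis.

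A second tempting inference is that the trial has 66% power. The document does not support that as a settled figure. Actual dropout is not reported because follow-up was still under way. The analysis is by intention to treat, girls who leave the intervention are encouraged to complete all assessments, and missing values are to be handled by multiple imputation or within the mixed model. The lower figures apply only if a fifth of outcomes are lost from the primary comparison, which is how the plan's own calculation treats dropout. Even with no loss, Fisher power is 77.3%.

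Third, a reader might conclude that the trial breaches its own floor of 50 per group. That figure is a recommendation cited from the literature, not a trial rule; the text does not say whether it counts girls randomised or analysed, and both allocated arms meet it.

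Finally, the shortfall is not hidden. The Results give 121, and the Abstract correctly calls 150 a target. The contradiction over numbers is confined to the closing paragraph of the Discussion. What is missing is any statement of what the shortfall means for power.

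**Conclusion.** The point holds as a mismatch between the power claim and the planned test, together with an internal contradiction over the number of participants. For 30% v 10%, two-sided .05, the planned Fisher test has 73.0% power at the intended 60 analysed per arm, about 7 percentage points below the stated 80%. With the 121 girls allocated it has between about 64% (20% lost from the analysis) and 77% (none lost). All these figures rest on the plan's assumed response rates, and the lower end also rests on its assumed dropout, applied equally to both arms. The description of 150 participants in the Discussion is wrong beside the 121 in the Results. The type I error rate and the choice of test are unaffected.

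**What to change.** - **Sample Size:** keep 150 as the a priori target. Add that the calculation corresponds to an uncorrected normal-approximation test (the authors should confirm this), and that the planned two-tailed Fisher exact test has about 73% power at 60 analysed per arm.
- **Results or limitations:** state that the target was missed (121 allocated, 64 and 57) and that Fisher power for 30% v 10% is about 64% to 77% depending on dropout. Note that fewer than 50 controls would be analysed if 20% drop out, and that the 50 is a cited recommendation.
- **Final paragraph of the Discussion:** replace the 150 participants by 121 randomised.

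No extra enrolment and no change of analysis is needed. The cost is a few sentences and a less favourable stated power.
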